### Data Analysis

Data analysis will be performed using SPSS (version 28.0.1; IBM Corp) software following the intention-to-treat approach. Descriptive statistics will be used to summarize the sociodemographic characteristics and clinical background of all participants. The homogeneity of baseline characteristics between the 2 groups will be tested by the Pearson chi-squared test or Fisher exact test, as appropriate. Linear mixed-effect models will be used to assess the intervention effects on the primary and secondary outcomes, with time (as a continuous variable), group, and the group-by-time interaction included as independent variables. Linear contrasts will be used to obtain between-group differences. The normality of the residuals and random effects will be assessed using normal probability plots. Missing values will not be replaced because mixed-effect models can accommodate participants with at least 1 outcome measurement [37]. A 5% level of significance will be adopted, with all significance tests being 2-sided.

For the qualitative data, all audio-taped interviews will be transcribed verbatim and managed by NVivo (version 12.0; Lumivero LLC). Two experienced qualitative researchers will carefully and inductively review the transcripts. A 5-step thematic analysis will be adopted [38]. The coded units will be sorted into categories and subcategories and analyzed to identify recurrent themes and patterns. This qualitative data will enhance the interpretation of the quantitative findings and help identify the strengths and weaknesses of the intervention being tested. An audit trail will be maintained to ensure data credibility. The coded data will be compared to identify discrepancies, and any disagreements will be resolved through discussion.

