**Methods:**

This assessor-blinded, 2-arm, randomized waitlist-controlled trial enrolled 132 individuals with PD and balance impairment, randomized to either the MY-PACE group (n=66, 50%) or the control group receiving routine outpatient care (n=66, 50%). The MY-PACE group will complete a 12-week, Zoom-delivered program incorporating mindfulness, yoga, and mindful walking practices. The control group will receive the intervention after study completion. The primary outcome is functional balance, as measured by the Berg Balance Scale. Secondary outcomes include functional mobility, gait patterns, balance confidence, freezing of gait severity, motor symptoms, anxiety and depressive symptoms, cognitive function, mindfulness, health-related quality of life, and fall incidence. Assessments will occur at baseline, 3 months (T1), and 6 months (T2). Data will be analyzed using linear mixed-effects models under the intention-to-treat principle.

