### Outcome Measures

Assessments are conducted at baseline (T0), 1 week after intervention (T1), and 3 months after intervention (T2) for all participants.

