The incidence, reasons, and consequences of falls are assessed monthly. A fall is defined as “an unexpected event in which you come to rest on the ground, floor, or other lower level.” Participants are contacted monthly by a trained research assistant using a structured interview format. During each follow-up, participants are reminded of the standardized fall definition and asked the following standardized questions: (1) whether any falls occurred in the preceding month, (2) the number of falls, (3) the circumstances surrounding each fall, and (4) whether any injury or medical attention resulted. To reduce recall bias, participants are encouraged to record falls prospectively during the study period.

Sociodemographic data are collected using a self-report questionnaire, including age, gender, marital status, educational level, religiosity, and financial status. In addition, clinical data, including time since onset, history of comorbidities (eg, hypertension and diabetes mellitus), history of psychiatric disturbances, treatment and medication records, and history of rehabilitation service use, are documented and considered control variables in the data analysis.

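### Fall incidence, a monthly count with no listed pre-randomization value, is assigned to a Gaussian linear mixed model that gives no incidence-rate comparison, and the term or contrast that tests it is not named

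*Protocol article*

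**What the plan says.** The abstract of the protocol article lists falls among the secondary outcomes: "cognitive function, mindfulness, health-related quality of life, and fall incidence". The Secondary Outcomes section sets their collection: "The incidence, reasons, and consequences of falls are assessed monthly". Each monthly interview records, among other items, "2) the number of falls".

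The Data Analysis section then gives one method for everything: "Linear mixed-effect models will be used to assess the intervention effects on the primary and secondary outcomes". The rest of that sentence names the terms: continuous time, group and their interaction. The section adds that linear contrasts will supply the between-group differences and that normality of residuals and random effects will be checked with probability plots. Falls are not excepted, and no count or rate model appears.

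The lead-in to Outcome Measures gives a general schedule: "Assessments are conducted at baseline (T0), 1 week after intervention (T1), and 3 months after intervention (T2) for all participants". The clinical background data are listed as "including time since onset, history of comorbidities (eg, hypertension and diabetes mellitus), history of psychiatric disturbances, treatment and medication records", followed by use of rehabilitation services. Neither place mentions a fall history or a fall count before randomization.

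**The concern.** The model suits a scale measured at T0, T1 and T2. The arms start level at T0, so a treatment effect appears as diverging lines and the group-by-time term is a natural summary. Falls are different in three ways.

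- They are non-negative counts, probably with many zeros, so normal residuals are unlikely.
- Incidence calls for a rate comparison, whereas the model returns a difference in mean counts or in slopes.
- No T0 value is listed, so the lines need not start together. A program that lowers a flat fall rate equally in every month gives parallel lines and no interaction.

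The model has other terms that would show such an effect. The article does not say which of them is the test for falls, and the answer to the fall question can depend heavily on that choice. Falls matter to this trial: the Background cites them as a consequence of balance impairment, and the Discussion names fall prevention as a use of the results.

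**Working it through.** **Inputs from the article.** 66 per arm with 20% anticipated attrition gives 66 × 0.8 = 52.8, so 53 per arm. There are about six monthly contacts up to T2. Tests are two-sided at 5%.

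**Assumed inputs.** The article gives no fall rate, dispersion or fall effect, so it has no figure of its own to reproduce. Control rates μ of 0.2, 0.5 and 1.0 falls per month were tried (0.4 in one further scenario), with rate ratios ρ of 0.7 and 0.5. Counts are Poisson with a gamma person effect of mean 1 and variance k (the dispersion), k = 1 or 2.

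**Step 1: what the interaction measures.** The model mean is β0 + β1·t + β2·G + β3·G·t. With a flat control rate μ and a reduction to ρμ from month 1, the arms differ by (ρ − 1)μ in every month. Hence β1 = 0, β2 = (ρ − 1)μ and β3 = 0. For μ = 0.5 and ρ = 0.5, β2 = −0.25 and β3 = 0. This is algebra and needs no simulation. A common T0 value would make the lines diverge, and β3 would not be zero.

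**Step 2: shape of the data.** For μ = 0.5 and k = 1:
- P(0) = (1 + kμ)^(−1/k) = 1/1.5 = 0.667
- variance = μ + kμ² = 0.75
- skewness = (μ + 3kμ² + 2k²μ³)/variance^1.5 = 1.5/0.75^1.5 = 2.31

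Simulated monthly counts gave 67% zeros and skewness 2.29.

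**Step 3: rejection rates, constant rate ratio 0.5.** There were 2000 replicates. Each person's slope and fitted value were compared by t-test, which for complete balanced data is equivalent to the mixed model with random slopes. The comparator is a Wald test of the log rate ratio on six-month totals with negative binomial variance.

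| Control rate | k | Group-by-time | Group term (month 0) | Month-3 contrast | Month-6 contrast | Rate-ratio test |
|---|---|---|---|---|---|---|
| 0.2 | 1 | 5.4% | 24.8% | 61.9% | 34.0% | 66.9% |
| 0.2 | 2 | 4.0% | 21.2% | 46.7% | 29.4% | 53.9% |
| 0.5 | 1 | 5.2% | 45.8% | 80.2% | 57.4% | 83.6% |
| 0.5 | 2 | 5.3% | 33.4% | 54.8% | 43.2% | 61.7% |
| 1.0 | 1 | 4.4% | 63.4% | 87.2% | 73.0% | 89.2% |
| 1.0 | 2 | 5.2% | 47.0% | 62.0% | 54.7% | 68.9% |

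For ρ = 0.7 the ranges are: group-by-time 4.1-5.6%, month-3 contrast 17.8-35.6%, month-6 contrast 11.7-29.8%, rate-ratio test 22.7-38.4%.

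A fitted random-intercept mixed model (0.5 falls per month, ρ = 0.5, 150 replicates) agreed: interaction 3%, group term 47%, mid-follow-up contrast 81%.

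**Step 4: a further scenario (0.4 falls per month, ρ = 0.5).** For k = 1, the month-3 contrast rejects 78%, the month-6 contrast 54% and negative binomial regression 80%. For k = 2 the figures are 54%, 39% and 56%.

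**Step 5: no effect.** In the Step 3 grid the interaction rejects 4.6-5.0%, the month-3 contrast 4.1-5.6%, the month-6 contrast 4.3-5.1% and the rate-ratio test 5.1-6.6%. The linear contrasts hold their size, and part of the rate test's small advantage is slight excess size.

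**Step 6: cost of the normal model alone.** At ρ = 0.5, comparing mean monthly counts loses between 1.3 points (87.9% against 89.2%) and 6.2 points (62.7% against 68.9%) to the rate-ratio test.

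**Step 7: a growing effect.** If the rate in month t is multiplied by 1 − t/7, the average multiplier is 1 − 3.5/7 = 0.5. At 0.5 falls per month and k = 1, the interaction then rejects 69%, the month-6 contrast 99.7% and the rate-ratio test 83.5%.

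**The case against.** The strongest reply is that the model is more than its interaction. Data Analysis also has a group term and promises linear contrasts. The Aims and Hypotheses section frames effects at T1 and T2, which points to contrasts at those times. A contrast near T1 performs almost as well as a rate model. A growing effect, quite plausible for a 12-week training program, would show in the interaction too. This stands. A reader might infer that the plan would report a real, constant reduction in falls as no effect; the article does not support that, because it does not make the interaction the sole test.

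Three other inferences also fail.
- That months of exposure are ignored after dropout. If each observed month is one row, each row carries one month of exposure and unobserved months add nothing. The problem arises only if counts are totalled, and the article does not say which is done.
- That normal-theory inference would be invalid. Under no effect the contrasts rejected close to 5%.
- That the fall data are already complete. The article says only that 132 participants are enrolled and that no outcome data have been analysed.

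The absence of a T0 fall count rests on a condensed list, so it can be called unlisted but not proven absent.

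One might add that an article leaves such detail to the analysis plan. That covers the choice of contrast in general. It does not cover a sentence that positively assigns falls to a linear model, in an article whose Results section says it reflects the prespecified analysis plan.

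**Conclusion.** The point holds at moderate severity. The article assigns a monthly count to a Gaussian linear mixed model that does not estimate an incidence rate ratio, and it does not say which term or contrast tests falls. Under a flat rate and a constant halving from month 1, that open choice moves power from about 5% (interaction) through 21-63% (group term) and 29-73% (month-6 contrast) to 47-87% (month-3 contrast), against 54-89% for a rate-ratio test. The loss from the normal distribution itself is only a few points.

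The zero interaction follows by algebra from three conditions: no T0 value, a flat rate, and an equal reduction from the first month. The percentages also rest on assumed rates and dispersions. A higher severity is not justified: falls are one of many secondary outcomes, the trial was sized only for the Berg Balance Scale, and that analysis is not touched. Even the better model has only 23-38% power at a rate ratio of 0.7.

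**What to change.** Take falls out of the linear mixed model sentence. State instead that the number of falls from randomization to T2 will be analysed by negative binomial regression, with group as the effect and log(person-months observed) as offset. Report the incidence rate ratio with its 95% CI. Report the proportion of participants with at least one fall as supportive. If the full analysis plan already names a count model for falls, align the article with it.

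The cost is one extra model for one secondary outcome, which can be fitted in SPSS, the named package, with its GENLIN procedure. It uses the monthly interviews already specified and changes nothing for participants. Since no outcome data have been analysed, a dated change made now would still be prespecified.

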### Aims and Hypotheses

This study aims to do the following:

Examine the effects of MY‑PACE, compared with usual care, on functional balance (primary outcome) and secondary outcomes, including functional mobility, balance confidence, freezing of gait (FOG) severity, motor symptoms, anxiety and depressive symptoms, cognitive function, mindfulness, HRQOL, and the incidence of falls over a 6‑month period in individuals with PDExplore participants’ experiences with MY‑PACE, including their practice of mindfulness yoga and factors influencing motivation, acceptability, and integration into daily life

It is hypothesized that participants with PD who receive the MY‑PACE intervention will demonstrate significantly greater improvements in functional balance at postintervention follow-up (T1) and at the 6‑month follow‑up (T2) compared with those receiving usual care. In addition, it is hypothesized that participants in the MY‑PACE group will show greater positive changes in secondary physical, psychological, and cognitive outcomes relative to the control group across the same time points.

The exploratory research question is as follows: What are participants’ experiences of using mindfulness yoga as a lifestyle intervention for balance management, particularly regarding perceived effects, perceived mechanisms of action (ie, how and why mindfulness may or may not work), and contextual factors influencing motivation, acceptability, and real‑life practice?

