## Methods

### Study Design

This study is a multicenter, assessor-blinded, 2-arm RCT using a sequential explanatory mixed methods design to evaluate the effectiveness and acceptability of a 12-week home-based mindfulness yoga program (MY‑PACE) compared with usual care. The study flow is presented in Figure 1 (CONSORT [Consolidated Standards of Reporting Trials] flow diagram). Outcomes will be assessed at 3 time points over 6 months: baseline prior to randomization (T0), 1 week after intervention (T1), and 3 months after intervention (T2).

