#### Usual Care

The usual care group continues routine outpatient services and receives an educational leaflet on general fall prevention and FOG management. Participants in this group will be offered the MY-PACE program after completion of the 6‑month study period.

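### Coding time as continuous forces the group difference onto a straight line, so the model cannot estimate the T1 and T2 effects separately, although the hypothesis names both

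*Protocol article*

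**What the plan says.** The Data Analysis section states: "Linear mixed-effect models will be used to assess the intervention effects on the primary and secondary outcomes". The fixed effects are specified "with time (as a continuous variable), group, and the group-by-time interaction included as independent variables". It then says: "Linear contrasts will be used to obtain between-group differences". No quadratic, piecewise or categorical time term is named.

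The Aims and Hypotheses section sets a target at each of two visits: the MY-PACE arm is expected to show "greater improvements in functional balance at postintervention follow-up (T1) and at the" 6-month follow-up (T2). Study Design places the assessments at "baseline prior to randomization (T0), 1 week after intervention (T1), and 3 months after intervention (T2"). The 12 weekly sessions therefore all fall between T0 and T1, and T1 to T2 is follow-up without sessions. Under Usual Care, controls "will be offered the MY-PACE program after completion of the" 6-month study period, so the arms stay distinct through T2.

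**The concern.** The hypothesis asks two questions: is there a benefit when the program ends, and is there one three months later? A model with one intercept difference and one slope difference gives a single answer spread along a line. It assumes that three months without sessions add as much benefit as the program itself. A program delivered entirely before T1 would more naturally produce a gain by T1 followed by a plateau or some loss, and neither shape is a straight line from baseline.

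The primary Berg Balance Scale result is at stake. If the group difference does not grow linearly, the T1 and T2 estimates are biased, a spurious difference appears at baseline, and a real end-of-program effect that fades can be missed by the group-by-time test. The same specification covers the secondary outcomes.

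**Working it through.** **Inputs from the protocol.** Visits at nominally 0, 3 and 6 months (Abstract; Study Design). Effect size 0.55 SD, 132 randomised 1:1, 20% attrition (Sample Size Calculation). Two-sided 5% level (Data Analysis).

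**Assumptions not in the protocol.** Within-person correlation rho = 0.5 (0.7 also shown), compound symmetry (AR(1) also shown), normal approximation for power.

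**The plan's own sample size.** For d = 0.55, two-sided 5% and 80% power, the exact two-sample t test needs 53 per arm (106), against the stated 110. The gap is on the safe side: 55 per arm gives 81.6%. After 20% loss, 132 × 0.8 = 105.6, or about 53 per arm, which is used below. The finding does not depend on this difference.

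**Step 1: what the model can represent.** Let d0, d1, d2 be the true group differences at T0, T1, T2. The planned model sets difference(t) = a + b·t. Centring time at 3 months gives −3, 0, +3, so

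b = (−3·d0 + 0·d1 + 3·d2) / 18 = (d2 − d0) / 6 per month.

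Per visit interval the weights on (T0, T1, T2) are (−0.5, 0, +0.5). The modelled change from baseline is 3b = (d2 − d0)/2 at T1 and 6b = d2 − d0 at T2. The T1 data do not enter the slope. These weights hold under compound symmetry and under AR(1).

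**Step 2: fitted values.** Under compound symmetry the fitted difference at the middle visit is the mean (d0 + d1 + d2)/3.

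| True difference (T0, T1, T2) | Fitted difference | Modelled change at T1 | Modelled change at T2 |
|---|---|---|---|
| 0, D, D (kept) | 0.17D, 0.67D, 1.17D | 0.50D (truth D) | 1.00D |
| 0, D, 0.5D (half lost) | 0.25D, 0.50D, 0.75D | 0.25D (truth D) | 0.50D |
| 0, D, 0 (all lost) | 0.33D, 0.33D, 0.33D | 0 (truth D) | 0 |
| 0, 0.5D, D (linear) | 0, 0.50D, D | 0.50D (correct) | 1.00D |

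Only the last pattern is recovered. With actual times of 13 and 24–25 weeks, the T1 change is fixed at 13/25 = 52% to 13/24 = 54% of the T2 change. With 20% of T2 missing, the modelled T1 change in the first three rows becomes 0.53D, 0.29D and 0.05D.

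**Step 3: power of the group-by-time test.** The standard error of a difference in change is sqrt(2(1 − rho) × 2/n). At rho = 0.5 and n = 53 this is sqrt(2/53) = 0.194 SD. Under compound symmetry the modelled T2 change has the same standard error.

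| Share of T1 effect kept at T2 | T2 change (SD) | Change / SE | Group-by-time power | Visit-specific T1 contrast |
|---|---|---|---|---|
| 100% | 0.550 | 2.83 | 81% | 81% |
| 75% | 0.4125 | 2.12 | 56% | 81% |
| 50% | 0.275 | 1.42 | 29% | 81% |
| 0% | 0 | 0 | 5% | 81% |

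At rho = 0.7 under compound symmetry the group-by-time power is about 95%, 45% and 5% for 100%, 50% and 0% kept, against about 95% for the T1 contrast. Under AR(1) with rho = 0.5, the 100% case falls from 81% to 64%.

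**The case against.** The strongest reply is that the protocol takes group differences from linear contrasts and does not say the slope test decides success. Software will print a T1 and a T2 contrast from this model. Contrasts of fitted levels also keep some power when the slope test has little: at rho = 0.5 under compound symmetry, about 21% at T1 and 17% at T2 if the effect is lost, 41% and 60% if half is kept, and 64% and 93% if all is kept. So a fading effect is not certain to be missed, and the powers in the table belong to the group-by-time test only. That stands. But both contrasts are functions of the same intercept and slope, so they are not separate estimates of the two effects, and at T1 they remain well below 81%. Random slopes do not help either, because the fixed-effect mean stays a straight line.

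Three further points are fair:
- Bias depends on the shape of the group difference. Curvature shared by both arms does no harm to the slope difference in complete data.
- The level 0.17D, 0.67D, 1.17D is specific to compound symmetry; AR(1) with rho = 0.5 gives 0.10D, 0.60D, 1.10D. The T1 change of 0.50D is the same under both.
- The protocol does not predict decay. It cites sustained benefit of meditation and intends continued self-practice. Under full maintenance and compound symmetry the slope test loses no power, but the T1 change is still halved.

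**Conclusion.** The concern holds. The protocol states a model that cannot give independent estimates of the two effects in its own hypothesis. This is an explicit choice of mean structure, not a detail left to a separate analysis plan. The T1 change from baseline is fixed at half the T2 change (52–54% on the week scale) whatever the T1 data show. It comes out at 0.50D, 0.25D or 0 for an effect fully kept, half kept or lost. Group-by-time power under these patterns is 81%, 29% and 5%.

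The straight-line constraint needs no assumption about correlation. The zero weight at T1 assumes balanced, equally spaced visits and compound symmetry or AR(1). The power figures also assume rho = 0.5, compound symmetry and 53 per arm. The true trajectory is unknown, which is a reason not to impose one. The point must be fixed before analysis because it affects the primary outcome.

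**What to change.** Replace the time clause in Data Analysis with wording such as: visit as a categorical factor (T0, T1, T2), group, and group-by-visit interaction, with an unstructured within-participant covariance; the between-group differences at T1 and at T2 are the group-by-visit contrasts. Apply it to the primary outcome and to all continuous secondary outcomes. State which of T1 and T2 is the primary contrast, or how the two are handled together. The unstructured covariance is a sensible default for three visits, but the essential change is to the mean model.

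The cost is a revised sentence, a different SPSS MIXED specification, one extra visit parameter and one extra interaction parameter, plus any added covariance parameters. The sample size does not change. Because the Results section presents the current text as the original prespecified plan and all 132 participants are enrolled, the change should be a dated, disclosed amendment. That section also says no outcome analyses have been done, so the amendment can still precede them.

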### Sample Size Calculation

Taking functional balance as the primary outcome, a meta‑analysis in individuals with PD reported a pooled mean difference of 3.64 (95% CI 2.06-5.22) points for resistance and balance training compared with control, corresponding to an estimated standardized effect size of Cohen *d*=0.66 [25], while a meta-analysis of cognitive-motor training in PD reported a standardized mean difference of 0.58 for balance outcomes compared with active or passive controls [26]. As this study will compare internally cued motor training with usual care, a conservative moderate effect size of 0.55 is assumed for the primary outcome. Using G*Power (version 3.1) for a 2‑arm parallel randomized controlled trial with a 2‑sided significance level of 0.05 and 80% power, 110 participants were required to detect an effect size of 0.55. Allowing for an anticipated attrition rate of 20%, a total sample size of 132 participants (66 per group) was recruited.

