### Procedure

Participants were recruited from local outpatient clinics and community organizations serving individuals with PD, including the Hong Kong Parkinson’s Disease Foundation, the Hong Kong Parkinson’s Disease Association, and the Community Rehabilitation Network. Study information and promotional materials were disseminated through online platforms and organizational networks. Potential participants were contacted by telephone or WhatsApp (Meta Platforms Inc) and screened for eligibility. Eligible individuals received a detailed explanation of the study via videoconference. Written informed consent was obtained in person prior to data collection. Following consent, baseline demographic and clinical assessments were conducted. All outcome assessments were performed during the participants’ self-reported medication “on” state to minimize the influence of motor fluctuations. Assessments were administered by trained research personnel who were blinded to group allocation. Participants were then randomly assigned in a 1:1 ratio to either the MY-PACE group (mindfulness-based, internally cued motor training) or the usual care group using a computer-generated randomization sequence. The allocation sequence was prepared by a researcher not involved in recruitment, intervention delivery, or outcome assessment. Group allocation was communicated to participants by an independent staff member to ensure allocation concealment. All outcome assessors remained blinded to group assignment throughout the study period.

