#### Primary Outcome

Functional balance is measured using the Berg Balance Scale (BBS). The BBS comprises 14 items evaluating balance performance during common daily activities, each rated on a 5‑point scale (0-4), yielding a total score ranging from 0 to 56. Scores of 0 to 20 indicate severe balance impairment, 21 to 40 indicate moderate impairment, and 41 to 56 indicate good balance. The BBS demonstrates excellent interrater (intraclass correlation coefficient=0.98) and intrarater reliability (intraclass correlation coefficient=0.98) and has been validated in individuals with PD [28].

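### The outcome model leaves the pre-randomization group difference in BBS free instead of using baseline BBS, so the treatment contrast is less precise than the data allow

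*Protocol article*

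**What the plan says.** Study Design sets the assessments at "baseline prior to randomization (T0), 1 week after intervention (T1), and 3 months after intervention (T2"). Under Primary Outcome, "Functional balance is measured using the Berg Balance Scale (BBS"), scored 0 to 56. Procedure says participants were "randomly assigned in a 1:1 ratio".

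Data Analysis gives one linear mixed model for the primary and secondary outcomes, "with time (as a continuous variable), group, and the group-by-time interaction included as independent variables", and adds: "Linear contrasts will be used to obtain between-group differences". It does not say whether the contrast compares levels at follow-up or changes from T0. The same section says the model can use anyone with at least one outcome measurement. This implies, without stating it, that T0 is one of the repeated responses.

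Outcome Measures lists clinical background items, such as time since onset, comorbidity, medication and rehabilitation use, as control variables. The baseline value of the outcome is not among them. Results says the article reflects the original prespecified analysis plan and that no outcome data have been analysed.

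**The concern.** Because T0 is measured before allocation, randomization makes the expected group difference at T0 zero. A group main effect plus a group-by-time term nevertheless treats that difference as unknown and estimates it. The data then do two jobs when only one is needed, and the treatment contrast pays in variance.

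Both contrasts that the wording allows are affected. A comparison of follow-up levels lets a chance difference in baseline BBS pass into the estimate. A comparison of changes subtracts the whole baseline difference, which is more than regression to the mean warrants once an imbalance has occurred. At stake are the width of the interval for BBS and for every continuous secondary outcome, and how far the primary result depends on chance baseline imbalance.

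**Working it through.** **Inputs.** Sample Size Calculation: "significance level of 0.05 and 80% power, 110 participants were required to detect an effect size of 0.55". That section then inflates for 20% dropout and arrives at 132, or 66 per arm. Data Analysis: "A 5% level of significance will be adopted, with all significance tests being 2-sided". Visits are taken as 0, 3 and 6 months. The correlation r is not given, so I assume 0.5 to 0.9 and also show 0.3 in the power check.

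**The plan's own figure.** An exact two-sample t test at d = 0.55 needs 53 per arm, or 106. Then 106/0.80 = 132.5, against the stated 132; also 110 × 1.2 = 132. Power with 55 per arm is 81.6%. The stated total is reproduced closely, and it assumes no baseline adjustment.

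**Single follow-up, as a power check.** The variance factors are 1 for level, 2(1−r) for change and 1−r² for baseline-adjusted. With 55 per arm, d = 0.55 and the normal approximation, the level contrast has SE √(2/55) = 0.191 and power 82.2%.

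| r | level | change | adjusted |
|---|---|---|---|
| 0.3 | 82.2% | 68.4% | 85.6% |
| 0.5 | 82.2% | 82.2% | 91.5% |
| 0.7 | 82.2% | 96.1% | 98.1% |
| 0.9 | 82.2% | >99.9% | >99.9% |

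**The article's own model: three visits, straight line, complete data.** With equally spaced visits the fitted T0-to-T2 change is the T2 value minus the T0 value. Its variance factor is 2(1−r) under compound symmetry and 2(1−r²) under AR(1), where r is the correlation between adjacent visits. Fixing the T0 difference at zero multiplies the variance by 1 − c², where c is the correlation between the fitted T0 difference and the change contrast. This reduces to:

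- compound symmetry: (2+4r)/(5+r)
- AR(1): 2/[2+(1−r)(3−r)]

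For example, at r = 0.5 these are 4/5.5 = 0.73 and 2/3.25 = 0.62. At r = 0.9 they are 5.6/5.9 = 0.95 and 2/2.21 = 0.90.

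The fitted T2 level has variance factor (5+r)/6 under compound symmetry, so the multiplier for the level contrast is 24(1−r)(1+2r)/(5+r)². The AR(1) level figures come from the generalized least squares variances.

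| r | change, CS | change, AR(1) | T2 level, CS | T2 level, AR(1) |
|---|---|---|---|---|
| 0.5 | 0.73 | 0.62 | 0.79 | 0.95 |
| 0.7 | 0.84 | 0.74 | 0.53 | 0.76 |
| 0.9 | 0.95 | 0.90 | 0.19 | 0.34 |

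Every multiplier is below 1. The change contrast gains most at low r and the level contrast most at high r.

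**Where power could fall short.** Under AR(1) with adjacent-visit r = 0.5, the T0–T2 correlation is 0.5² = 0.25. Power for d = 0.55 at T2 is then 65% for the change contrast and 85% with a common T0 mean. This agrees with the single-follow-up table: the change contrast drops below plan when the correlation between the two visits compared is under about 0.5.

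**Chance imbalance.** Under compound symmetry the fitted T2 level weights the three visits −1/6, 1/3 and 5/6. A chance T0 difference D therefore leaves (−1/6 + r/3 + 5r/6)D = (7r−1)D/6 in the expected level contrast, which is 0.65D at r = 0.7. The change contrast leaves −(1−r)D, or −0.30D.

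**The case against.** The strongest reply is that this is a common and valid longitudinal model. Over repeated randomizations its contrasts are not biased by the free T0 term, and the sample size was set without counting on baseline adjustment. That stands. A reader might infer bias or an underpowered trial, and the documents support neither: a level contrast keeps about 82% power, and a change contrast keeps at least that once r reaches about 0.5.

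A reader might also take the large level-contrast gains, or single-visit power gains at T1, as the size of the problem. The article does not choose a level contrast. Its hypothesis of greater improvement and its interaction term point to change, where the gain is smaller. Single-visit formulas also do not describe T1 in a straight-line model, which borrows from all three visits.

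Finally, a condensed article may leave covariates and contrasts to a full plan, and T0 as a response is inferred. This tempers confidence but does not remove the point. The fixed effects are stated, they are said to reflect the prespecified plan, and the named control variables do not include baseline BBS. If T0 were not a response, baseline BBS would go unused and the level-contrast loss would apply.

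**Conclusion.** The point holds as an avoidable loss of efficiency, worth correcting but not a flaw in validity. For the change contrast in the article's own model, the variance that a common T0 mean would remove is about 27% at r = 0.5 falling to 5% at r = 0.9 under compound symmetry, and 38% falling to 10% under AR(1). For the T2 level contrast it is 21% rising to 81%, or 5% rising to 66%, and the estimate would also be exposed to chance baseline imbalance.

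These sizes rest on an assumed r, equal variances across visits, complete data and T0 being a response. The direction is the same in every case computed. At high r with a change contrast the practical gain is small.

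**What to change.** Before any outcome analysis, record a dated amendment covering BBS and all continuous secondary outcomes, with one of two specifications:

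- **Common T0 mean.** Code time as 0 at T0, drop the group main effect and keep the group-by-time term or terms.
- **Baseline as covariate.** Model T1 and T2 only, with the baseline value of the same outcome and its interaction with visit as covariates.

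In either case, name the between-group contrast and the visit to which it refers. The first option can keep the straight-line time coding; whether that coding is suitable is a separate question.

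The cost is analysis wording and the amendment. No further participants, visits or data are needed, since baseline values are already collected.
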